| Risk analysis                                                                                          | The risk-classification is assessed as low / moderate to the study population receiving study drug at the current regimen. Lanadelumab has a favorable safety profile and is approved by the Dutch medicines evaluation board for the dose administered. Therefore the risk for adverse events is low.                                                                                                                                                                                                                                                                                                                                                                                                                                                                                                                                                                                                                                                                                                          |
| Nature and extent of the burden and risks associated with participation, benefit and group relatedness | 
The study participants are COVID-19 patients that might benefit from the participation in this clinical trial.
 
Participants are on the ward of the time of study
 
Burden: short visits (15 minutes) several time per day on the ward by doctor and nurse for clinical evaluation. The duration of the entire trial (excluding screening period) is 14 days. Duration of treatment with study medication is 2 days.
 
Lanadelumab has a generally favorable safety profile. We refer to the SmPC for most common side effect.
 
For pharmacokinetic purposes 14 blood samples will be taken in total in the intervention group only. For a total of 28 mL. Additional samples will be taken for biomarker evaluation (two occasions of 40mL each).
 
Safety assessment (haematology, clinical chemistry, blood glucose tests, hCG blood and hCG urine tests, serology) will be collected as part of routine care. The total blood volume taken will be approximately 100 mL..
 |

| ANALYTICAL AND
STATISTICAL
METHODS |                                                                                                                                                                                                                         |

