## 4. Treatment

In the current study subjects will be treated with lanadelumab 300 mg IV on day 1 followed by a second dose of lanadelumab 300mg IV on day 4.

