### 5.3 Method of assigning subjects to treatment groups

Subject will be randomized in a 1:1 ratio to receive lanadelumab or standard clinical management without drug intervention. Each group will contain 20 participants.

Randomization will be done by Castor. Each patient will be entered into the Castor system and randomization will be allocated immediately. This is a standard procedure as deployed in other trials.

Each site has drug on site for at least one patient and therefor randomisation to the intervention arm can be acted upon immediately. Considering the small sample size there will be no stratification.

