## 6. Study procedures

### 6.1 Inclusion Screening and screening during treatment

At inclusion screening the medical history of the subject will be verified and documented to establish eligibility for inclusion. In table 2 a summary is listed of the parameters that should be collected at baseline and while on treatment.

Table 1: summary of study procedures during the study

|                                                    | At inclusion | Day 1 | 2 | 3 | 4 | 5 | 6 | 7 | 8-14 | >14 |
|----------------------------------------------------|--------------|-------|---|---|---|---|---|---|------|-----|
| Demographics a                          | X            | X     |   |   |   |   |   |   |      |     |
| Physical examination b                  | X            | X     |   |   |   |   |   |   |      |     |
| Laboratory tests c                      | X            | X     | X | X | X | X | X | X | X    | X   |
| Administration lanadelumab intervention group only |              | X     |   |   | X |   |   |   |      |     |
| Oxygen need d                           | X            | X     | X | X | X | X | X | X | X    | X   |
| Concomitant medication                             | X            | X     | X | X | X | X | X | X | X    | X   |
| Clinical outcome                                   | X            | X     | X | X | X | X | X | X | X    | X   |
| PK e                                    |              | X     | X | X | X | X | X | X | X    |     |
| PD & in depth sampling f                |              | X     |   |   | X |   |   |   |      |     |

a: sex, age, BMI, days of illness, Charlson Comorbidity Index (CCI), comedication, CT severity score, oxygen saturation without supplementation, oxygen supplementation need, respiratory rate at baseline.

b: respiratory rate, oxygen saturation, and supplemental oxygen.

c: hemocytometry, WBC differentiation, D-dimer, ferritin, CRP, and albumin. EDTA plasma 10 mL and citrate 4 mL for plasma kallikrein metabolites.

d: change in oxygen need and oxygenation expressed as absolute number of liters per hour using a target oxygenation of above 94% as a marker of pulmonary status. ICU admission after admission to the ward, changes in D-dimer relative to baseline, PKa metabolites changes relative to baseline, safety.

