e determination of lanadelumab plasma concentration (pk outcome, intervention group only) and bradykinin markers (PD outcome. ) PK after first lanadelumab administration: T1=12-24; T2 = T1 + 24 (+/-6 hours); T3= T1+ 48 (+/-6 hours); T4= T1 + 72 (+/-6 hours); T5= T1 + 96(+/-6 hours); T6 = T1 + 120 (+/-6 hours); T7 = T1 + 144 (+/-6 hours) and then daily. If only one lanadelumab dose is given PK will be sampled up to and including day 7, or until patient is dismissed from the hospital whichever comes first.

f Determination of bradykininemarkers and in-depth sampling. Labsampling day 1 needs to be done before first administration of lanadelumab. Day 4 has a window of +/- 2 days if day 4 is in the weekend. Blisters for day 1 and 4 include 2x 10 ml EDTA, 2x 4 ml citrate and 1 PAXgene for in depth labanalysis., See also the labmanual.

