### Data and outcome variables:

Data on clinical parameters including respiratory rate, oxygen saturation, and supplemental oxygen are registered before and after administration of lanadelumab and then daily. Changes in oxygen support requirement and clinical symptoms are recorded. Laboratory tests are performed during the study: hemocytometry, WBC differentiation, D-dimer, ferritin, CRP, and albumin (Table 1).

Kinins, biomarkers, and functional immunological profiling will be assessed in the forty randomized patients with EDTA plasma (10ml), PBMCs (20ml EDTA), mass spectrometry (2ml blood in specialized medium tube), and citrate plasma (8ml), with a total volume of 40ml per in depth sampling.

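### The weekend window for the day-4 biomarker sample spans the second infusion, so the protocol permits this sample to follow one dose in some treated patients and two in others

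*Protocol*

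**What the plan says.** Table 1 in Protocol section 6.1 marks PD and in-depth sampling on day 1 and day 4 only. The synopsis likewise gives two biomarker occasions. The second infusion is marked on that same day 4, and section 4 has it as "followed by a second dose of lanadelumab 300mg IV on day 4". The synopsis and sections 3.1, 4.1 and 4.3 give the same day, and none gives a window.

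Footnote f fixes the baseline sample relative to dosing: "Labsampling day 1 needs to be done before first administration of lanadelumab". For the follow-up sample it gives only this: "Day 4 has a window of +/- 2 days if day 4 is in the weekend". It then refers to a lab manual, which is not available here.

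Under Data and outcome variables, the protocol states: "Kinins, biomarkers, and functional immunological profiling will be assessed in the forty randomized patients". On arm size, section 5.3 says: "Each group will contain 20 participants".

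**The concern.** The baseline sample is tied to the first dose, but the follow-up sample is not tied to the second, although both are scheduled for the same day. At weekends the sample may move two days either way while the infusion has no stated allowance to move. The window therefore crosses a dosing event.

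If samples are taken on both sides of that event, the change from day 1 to day 4 in the treated arm is a blend of a one-dose and a two-dose response. That adds spread within the treated arm only, because controls have no second dose. It also leaves the contrast between arms without one clear meaning. In both arms the window lets time since baseline vary as well. With 20 treated patients, splitting by side of the infusion would leave small groups. An analysis plan cannot repair a sample drawn on the wrong side of a dose.

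**Working it through.** The protocol gives no sample size or precision figure for the biomarkers, so there is no figure to reproduce. The check has three parts.

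**1. Permitted timing.** Inputs: sample on day 4 ± 2 days at weekends (footnote f); infusions on days 1 and 4 (section 4).

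| Day 4 falls on | Moved to | Study day | Days since dose 1 | Doses received |
|---|---|---|---|---|
| Saturday | Thursday | 2 | 1 | one |
| Saturday | Friday | 3 | 2 | one |
| Saturday | Monday | 6 | 5 | two |
| Sunday | Friday | 2 | 1 | one |
| Sunday | Monday | 5 | 4 | two |
| Sunday | Tuesday | 6 | 5 | two |

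Every row conforms to footnote f. If the sample stays on day 4 itself, whether at a weekend or on a weekday, it may be drawn on either side of the infusion.

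**2. Exposure on each side of the second dose.** Inputs: predicted Cmax after 300 mg IV of 94.1 µg/mL and half-life of about 15 days (both section 1.2). Single-exponential approximation: C(t) = 94.1 × 2^(−t/15), with t in days since dose 1, adding 94.1 at the second dose.

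- Day 2: 94.1 × 2^(−1/15) = 89.9
- Day 3: 94.1 × 2^(−2/15) = 85.8
- Day 4, before dose 2: 94.1 × 2^(−3/15) = 81.9
- Day 4, after dose 2: 81.9 + 94.1 = 176.0
- Day 5: 176.0 × 2^(−1/15) = 168.1
- Day 6: 176.0 × 2^(−2/15) = 160.5

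The ratio runs from 160.5/89.9 = 1.8 to 176.0/81.9 = 2.1, so about two-fold. Section 1.2 also gives a half-life of about 14 days; with that value the level before dose 2 is 94.1 × 2^(−3/14) = 81.1, which changes nothing of substance. These are drug concentrations, not marker levels.

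**3. How many treated patients fall under the window.** The protocol does not give the weekday pattern of enrolment. Assuming day 1 is spread evenly over the week, 2/7 of patients have day 4 in a weekend. Then 20 × 2/7 = 5.7 treated patients, with a central 95% binomial range of 2 to 10. The chance that at least one is affected is 1 − (5/7)^20 = 0.999.

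**The case against.** The strongest reply is that this sample does not carry the pathway PD alone. A reader might infer from Table 1 that day 4 is the only follow-up for bradykinin markers. The documents do not support that: footnote e names bradykinin markers with the PK row, marked through days 8–14, and footnote c lists tubes for plasma kallikrein metabolites with the laboratory row, marked throughout. This objection stands. It confines the full force of the point to the in-depth set, which has no other follow-up.

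Second, the lab manual may already require a draw before infusion. That is possible, so mixing is permitted by the protocol and not certain. But such a rule would conflict with the later half of the weekend window unless the dose moved too, and no section says that it does.

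Third, the two-fold figure could be read as a PD effect. It is not one. The approximate level before dose 2, 81.9 µg/mL, is already about 2.4 times (81.9/34) the subcutaneous Cmax of 34 µg/mL that section 1.2 associates with sufficient exposure in HAE. HAE is a different disease, so this does not prove a plateau, but the added spread in the markers may be small.

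Fourth, treated patients have frequent PK samples and mixed-effects modelling is planned (synopsis), PK samples carry date and time (section 10.1), and administration is recorded (section 5.5). Exposure at the sampling time could therefore be estimated. This helps the treated arm, but it does not give the sample a defined position, and with so few patients the separation of dose number from elapsed time would rest heavily on the model.

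Finally, the primary objectives are symptom relief and safety (section 1.3) and the primary endpoint is oxygen use (section 7.3). No primary conclusion depends on this sample.

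**Conclusion.** The point holds as a minor but real flaw in a stated sampling rule. When day 4 is in a weekend, footnote f permits the PD and in-depth sample from day 2 to day 6, across an infusion fixed on day 4, and it sets no position relative to that infusion on any day. About 6 of 20 treated patients (range 2 to 10) would fall under the window if enrolment is even over the week. Exposure differs about two-fold across the second dose under a single-exponential approximation. The consequence for the markers cannot be sized from the protocol.

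A reader might also infer that all 20 treated patients are affected, because the missing pre-dose rule applies to each of them. That does not follow: if every day-4 sample were drawn on the same side of the infusion, nothing would be mixed. The weekend window is the firmer part of the point, because a pre-dose rule in the lab manual could settle ordinary weekdays but not samples moved later. The weight is that of an exploratory outcome, and the point is worth acting on because the remedy is cheap.

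**What to change.** In footnote f, and in the lab manual to match:

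- Require the day-4 PD and in-depth sample before the second infusion in treated patients, and at the matching study time in controls.
- If day 4 is in a weekend, let the sample move earlier only, to day 2 or 3.
- Record clock times of this sample and of the infusion.
- Account for actual time since dose 1 in the analysis, using the matching study time in controls.

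This changes sampling only. The cost is a narrower weekend window, with some samples taken as early as day 2. A Sunday day 4 moved to Friday is only one day after the first dose, so some spread in elapsed time replaces the spread in number of doses, and matched controls have the same shorter follow-up. That is why the last item is needed.

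If the sponsor meant the infusion to move together with the sample, footnote f and the sections that fix the second dose on day 4 must be reconciled.

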### Oxygen supply treatment procedures:

[figure not shown]

A well-established standardized protocol published in NEJM which follows the approach in the flow diagram of conservative oxygen therapy, which is based on titrating on the lowest acceptable SpO2 with 30 min intervals will be used. (The ICU-ROX Investigators and the Australian and New Zealand Intensive Care Society Clinical Trials Group. N Engl J Med 2020;382:989-998)

### Data and outcome variables:

Data on clinical parameters including respiratory rate, oxygen saturation, and supplemental oxygen are registered before and after administration of lanadelumab and then daily. Changes in oxygen support requirement and clinical symptoms are recorded. Laboratory tests are performed during the study: hemocytometry, WBC differentiation, D-dimer, ferritin, CRP, and albumin (Table 1).

Kinins, biomarkers, and functional immunological profiling will be assessed in the forty randomized patients with EDTA plasma (10ml), PBMCs (20ml EDTA), mass spectrometry (2ml blood in specialized medium tube), and citrate plasma (8ml), with a total volume of 40ml per in depth sampling.

## 6.2 Safety assessments

Safety assessments will be recorded as part of this trial.

## 6.3 Safety reporting

The methods of this study are considered as limited risks. In the unlikely event that a patient dies due to the lanadelumab treatment this will be reported to the ethical committee via toetsingonline.nl. The investigator must assess the causality of death. In case there is clear evidence that suggests a causal relationship this will be reported to the sponsor on a SAE form.

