#### ***Serious Adverse events (SAEs)***

A serious adverse event is any untoward medical occurrence or effect that

- results in death;
- is life threatening (at the time of the event);
- requires hospitalisation or prolongation of existing inpatients' hospitalisation, admittance to the Intensive Care Unit due to respiratory insufficiency will not be reported as an SAE;
- results in persistent or significant disability or incapacity;
- is a congenital anomaly or birth defect; or
- any other important medical event that did not result in any of the outcomes listed above due to medical or surgical intervention but could have been based upon appropriate judgement by the investigator.

The investigator in a participating center will report all SAEs to the coordinating investigator without undue delay after obtaining knowledge of the events.

The sponsor will report the SAEs through the web portal *ToetsingOnline* to the accredited METC that approved the protocol, within 7 days of first knowledge for SAEs that result in death or are life threatening followed by a period of maximum of 8 days to complete the initial preliminary report. All other SAEs will be reported within a period of maximum 15 days after the sponsor has first knowledge of the serious adverse events.

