***Suspected unexpected serious adverse reactions (SUSARs)***

Adverse reactions are all untoward and unintended responses to an investigational product related to any dose administered.

Unexpected adverse reactions are SUSARs if the following three conditions are met:

1. the event must be serious;
2. there must be a certain degree of probability that the event is a harmful and an undesirable reaction to the medicinal product under investigation, regardless of the administered dose;
3. the adverse reaction must be unexpected, that is to say, the nature and severity of the adverse reaction are not in agreement with the product information as recorded in:
  - Summary of Product Characteristics (SPC) for an authorised medicinal product;
  - Investigator's Brochure for an unauthorised medicinal product.

The investigator in a participating centre will report the SUSAR to the coordinating investigator.

The coordinating investigator will report expedited the following SUSARs through the web portal *ToetsingOnline* to the METC:

- SUSARs that have arisen in the clinical trial that was assessed by the METC;
- SUSARs that have arisen in other clinical trials of the same sponsor and with the same medicinal product, and that could have consequences for the safety of the subjects involved in the clinical trial that was assessed by the METC.

The remaining SUSARs are recorded in an overview list (line-listing) that will be submitted once every half year to the METC. This line-listing provides an overview of all SUSARs from the study medicine, accompanied by a brief report highlighting the main points of concern.

The expedited reporting of SUSARs through the web portal Eudravigilance or ToetsingOnline is sufficient as notification to the competent authority.

The sponsor will report expedited all SUSARs to the competent authorities in other Member States, according to the requirements of the Member States.

The expedited reporting will occur not later than 15 days after the sponsor has first knowledge of the adverse reactions. For fatal or life threatening cases the term will be maximal 7 days for a preliminary report with another 8 days for completion of the report.

**For individual sites, the local investigator completes the SAE report in Castor and providing as much detailed information as known and relevant to the event within 24 hours of discovery of the event.**

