**The coordinating investigator will automatically be notified via Castor by email when a new SAE is reported in Castor. If there are technical issues with Castor the local investigator completes the SAE report on paper. A template of this report will be provided in de ISF. The sponsor will report all SAEs using the CCMO module 'ToetsingOnline' to the accredited METC that approved the protocol. By means of this website notifications will be sent to the relevant authorities (METC/LAREB/EudraVigilance). The reporting will occur within 15 days after the investigator has first received information on the SAE. For fatal or life-threatening cases a preliminary report will be offered within 7 days followed by a complete report within 8 days. SUSARs will be electronically reported via ToetsingOnline and the trial coordinator will communicate all SUSARs to the independent monitor of this study.**

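### Section 6.3 gives two rules for reporting a death: its opening paragraph ties the SAE form to clear evidence of a lanadelumab cause, while its SAE rules cover every death in both arms

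*Protocol*

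**What the plan says.** Section 6.3 deals with deaths twice.

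Its opening paragraph starts with the ethics committee: "In the unlikely event that a patient dies due to the lanadelumab treatment this will be reported to the ethical committee via toetsingonline.nl". Next comes a causality assessment by the investigator, and the paragraph ends: "In case there is clear evidence that suggests a causal relationship this will be reported to the sponsor on a SAE form".

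The subsection on serious adverse events sets no causality condition. It begins "A serious adverse event is any untoward medical occurrence or effect that", and death is the first outcome on its list. On scope it says: "The investigator in a participating center will report all SAEs to the coordinating investigator without undue delay after obtaining knowledge of the events". For the sponsor's report to the ethics committee (METC), it gives a limit for fatal and life-threatening events, "within 7 days of first knowledge for SAEs that result in death or are life threatening", with up to 8 further days to complete the report. For the rest: "All other SAEs will be reported within a period of maximum 15 days after the sponsor has first knowledge of the serious adverse events".

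The closing text of the section, after the SUSAR rules, has the local investigator file the SAE report in Castor with "as much detailed information as known and relevant to the event within 24 hours of discovery of the event". The coordinating investigator is notified automatically, and the sponsor is to report all SAEs to the METC. It restates the 15-day limit with another starting point: "The reporting will occur within 15 days after the investigator has first received information on the SAE".

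**The concern.** The opening paragraph is the only text in the section devoted to death, so a site could reasonably take it as the specific rule and the SAE subsection as the general one. Read that way, it makes causality a condition for filing the form. A death attributed to COVID-19 would not meet the condition, and a death in the control arm never could.

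Demonstrating the safety of intravenous lanadelumab is a primary objective (Section 1.3), and Section 9.1.4 says that safety information for this route comes only from modelling and simulation. The trial is open-label, so causality is judged with the arm known. Other safety channels are also filtered: adverse events are recorded only where a drug effect is reasonably suspected, ICU admission for respiratory insufficiency is exempt from SAE reporting, and the stopping rule in Section 3.7 needs an event attributable to lanadelumab. Death is one of the few outcomes that the SAE rules collect in both arms without a causality test. The sponsor's duty in Section 6.3 to suspend the study on safety grounds depends on those reports arriving on time.

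**Working it through.** There is no stated figure to reproduce: Section 7.1 says that no formal sample size calculation was done, and the protocol gives no mortality rate. The check is a comparison of texts.

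**Which deaths are reported**

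| Question | Opening paragraph of 6.3 | SAE subsection and closing text of 6.3 |
|---|---|---|
| Form from the site | Where there is clear evidence of a causal link | Every SAE, and death is an SAE |
| Report to the ethics committee | A death due to lanadelumab is named | All SAEs |
| Causality condition | Yes | None |
| Time limit | None given | 24 hours for Castor entry; 7 days plus 8 for a fatal event |

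Two cases show the difference.

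1. A lanadelumab patient dies and the site attributes the death to COVID-19. The opening paragraph calls for no form. The later rules call for a Castor report within 24 hours and a METC report within 7 days.
2. A control patient dies. No lanadelumab was given, so the opening condition cannot be met. The later rules apply in full.

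As a count of patients (Section 5.3: 20 per arm), 20/40 = 50% of those randomized can never meet the opening condition, while 40/40 = 100% fall under the later rules. This is a count of patients covered, not of deaths missed.

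The section exempts one event from SAE reporting, ICU admission for respiratory insufficiency. Death is not exempted, and no sentence ranks the two rules.

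**The 15-day clock (a separate point)**

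The SAE subsection counts the 15 days from the sponsor's first knowledge; the closing text counts them from the investigator's first information. These can be different dates for the same report. For fatal events the two texts agree on the lengths, 7 days and then 8, so the differing 15-day start does not bear on deaths.

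**The case against.** The opening paragraph never says that a form is filed only when causality is clear. It can be read as describing what happens when a death is attributed to the drug, with silence about other deaths. The detailed rules follow in the same section and are explicit: death heads the SAE list, all SAEs are reported, Castor entry is due within 24 hours, and the sponsor passes all SAEs to the METC. The authors considered exemptions and did not exempt death. For a death to go unreported, a site would have to let one introductory sentence override several explicit ones. Deaths could also show up in the clinical outcome data of Table 1, and the yearly METC report lists serious adverse events.

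Much of this stands. It limits the consequence to a possibility that depends on how a site reads the section. It does not remove the contradiction, because a causality condition that is meant to have no effect should not be in the text. Outcome data and a yearly report do not replace the 24-hour and 7-day limits.

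It is also fair that an imbalance in deaths would be hard to establish at 20 per arm. Four deaths against none gives a two-sided Fisher p of 2 × C(20,4)/C(40,4) = 2 × 4,845/91,390 = 0.106. The reason to collect every death is therefore prompt review of each case in both arms, not a formal comparison.

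**Conclusion.** The contradiction on deaths is real and should be corrected. Its effect is conditional: deaths attributed to COVID-19 and control-arm deaths could be withheld by a site that follows the opening paragraph, and would all be reported by a site that follows the SAE rules. This rests on taking the opening sentence as a condition, which is its natural reading but not its literal wording.

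Three stronger readings are not supported.

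- A reader might infer that the protocol permits control-arm deaths to go unreported. Its explicit SAE rules require the opposite.
- A reader might put a number on the deaths missed. That would need an assumed mortality combined with the least favourable reading at every site, and the document supplies neither.
- A reader might see a conflict between prompt reporting in the SAE subsection and 24 hours in the closing text. The second makes the first specific, and one report satisfies both.

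The two starts of the 15-day clock are a genuine but lesser inconsistency. With 24-hour Castor entry and automatic notification they should lie about a day apart, and a report that meets the earlier limit meets both.

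**What to change.** Reword the opening paragraph of Section 6.3 so that every death in either arm, whatever its presumed cause, is reported under the section's own SAE rules: Castor entry within 24 hours and a METC report within 7 days, completed within 8 more. Keep the investigator's causality assessment as an item on the form, and remove it as a condition for filing.

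Separately, choose one starting point for the 15-day METC report and use it in both the SAE subsection and the closing text.

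Both are wording changes that leave the design and data collection as they are. The cost is a few extra SAE forms at most, and none at sites that already follow the SAE rules.
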